#### Medical Outcomes (WittyFit Research)

WittyFit is based on two databases: WittyFit, which deals with behavioral data, and WittyFit Research, which deals with medical data. To guarantee the highest level of security, the two databases are separate and do not interact; physicians from the University Hospital of Clermont-Ferrand will be the only researchers with access to medical data. Behavioral data (WittyFit) are those within the three major health-related categories: physical, mental, and work-related well-being. Medical data (WittyFit Research) are medical history and chronic diseases classified using the International Classification of Diseases, medications classified using the Anatomical Therapeutic Chemical classification, any clinical data known by participants such as heart rate or blood pressure, and the most common biological data such as blood glucose levels, hemoglobin A_1c_, or blood cholesterol levels (Textbox 1).

Parameters measured.Data retrieved from self-reported questionnaires:WittyFit—behavioral data:Physical health:NutritionPhysical activitySleepMusculoskeletal functionMental health:StressMoodAddiction (to be added)Work-related health:Job strainLatitude/decision-makingWork orgainzation and tasksSocial supportRecognitionWittyfit Research—medical data:Medical history and chronic diseases classified using the International Classification of DiseasesMedications classified using the Anatomical Therapeutic Chemical classificationClinical data known by participants, such as:Heart rateBlood pressureCommon biological data known by participants, such as:Blood glucose levelHemoglobin A_1c_Blood cholesterol levelData retrieved from companies—economic data:Continuously monitored:Occupation, type of contractBenefitsSales revenueAbsenteeismTurnoverProductivityWhen a worker (identified by human resource–generated number) disappears:RetirementRelocation to another companyDeath (premature mortality)

### Objectives

The shorter term objectives will be to demonstrate that WittyFit improves parameters of well-being and morbidity based on three major health-related behavioral categories. The mid-term objectives will be to demonstrate that WittyFit improves economic data of the companies such as productivity and benefits. The primary long-term objective will be to demonstrate that WittyFit will contribute to decrease premature mortality.

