**Methods:**

This is an exploratory interventional cohort study in an ecological situation. Three groups of participants will be purposefully sampled: employees, middle managers, and executive managers. Four levels of engagement are planned for employees: commencing with baseline health profiling from validated questionnaires; individualized feedback based on evidence-based medicine; support for behavioral change; and formal evaluation of changes in knowledge, practices, and health outcomes over time. Middle managers will also receive anonymous feedback on problems encountered by employees, and executive top managers will have indicators by division, location, department, age, seniority, gender and occupational position. Managers will be able to introduce specific initiatives in the workplace. WittyFit is based on two databases: behavioral data (WittyFit) and medical data (WittyFit Research). Statistical analyses will incorporate morbidity and well-being data. When a worker leaves a workplace, the company documents one of three major explanations: retirement, relocation to another company, or premature death. Therefore, WittyFit will have the ability to include mortality as an outcome. WittyFit will evolve with the waves of connected objects further increasing its data accuracy. Ethical approval was obtained from the ethics committee of the University Hospital of Clermont-Ferrand, France.

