### Outcomes

#### Behavioral Outcomes: Three Major Health-Related Categories (WittyFit)

Workers will answer validated questionnaires within three major health-related behavioral categories: physical, mental, and work-related well-being (Textbox 1). Each main category is divided in subcategories:

Physical well-being investigates nutrition, physical activity, sleep, and musculoskeletal function. Nutrition will be assessed through 24-hour recalls of food intake. Physical activity combines questions about time spent in activity at work and leisure, as well as estimates of sedentary behavior time. This category also includes a questionnaire on sleep quality and quantity [46]. Musculoskeletal function is based on an adapted version of the Nordic Musculoskeletal Questionnaire [64].Mental well-being explores stress and mood. We will use the validated Hospital and Anxiety Depression Scale [65] and the visual analog scale of stress [66,67]. Questions on smoking and addiction will be added later.Work-related health questions explore job strain, latitude/decision-making, work organization and tasks, social support, and recognition. We will use the validated Job Demand-Control-Support model of Karasek [18-20] and the effort reward model of Sieigrist [21-23] with the addition of some specific questions such as visual analog scales (demand, control, etc) that we want to further validate.

Participants complete questionnaires at times convenient to them; however, participants will be prompted to complete a general visual analog scale from the main categories and major subcategories every 15 days and the more detailed questionnaires every 6 months. When a significant difference appears on the latest visual analog scale, the user is asked to complete specific questionnaires linked with the problem detected by the visual analog scale. Gaming and trophies are incentive strategies for workers to fulfill questionnaires.

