### Statistical Considerations

#### Sample Size Calculations

Using only Internet or computer interventions for behavior change outcomes improving eating disorders and nutrition [76], weight and cardiorespiratory fitness [77], or mood [78] and stress related to the workplace and performance and productivity [79], the sample size estimation was performed according to Cohen’s recommendations with the following defined effect size (ES) bounds: small (ES 0.2), medium (ES 0.5), and large (ES 0.8, “grossly perceptible and therefore large”) [80]. Considering an effect size of 0.33, a 2-tailed type I error fixed at a=0.001 to take into account multiple comparisons, and a moderate loss to follow-up rate, N=1000 participants will allow us to highlight (1) such ES for a statistical power greater than 95% for paired comparisons (n=225 with a correlation coefficient of .5) and (2) such ES for a statistical power greater than 80% for intergroup comparisons (n=311 by group).

For life expectancy, 100,000 workers followed over 5 years would provide a sufficient and relevant sample size to achieve the long-term objectives measured by this study. Purposive sampling will be conducted to best draw comparisons with previous research [81] studying leisure time spent sitting in relation to total mortality in a prospective cohort of US adults [9] and to further elucidate job strain among blue-collar and white-collar employees. Job strain has previously been associated with total mortality in a 28-year cohort study [82]. To address the objective of reducing premature mortality, statistical power estimation was based on a hazard ratio used for censored data (hazard ratio of 1.25 and 2) and in accordance with previously described data. This hazard ratio estimate was proposed to support a type I error of 5% (2-sided) with statistical power at 95% (see Figure 7). However, the study will be unlimited within the long-term aspects of its epidemiological design.

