#### Analyses of Shorter Term Objectives

To study WittyFit’s effect on morbidity and well-being, analyses will include comparisons with historical cohorts and literature and within the paired data from individual participants as they generate their own basis for comparison. To study longitudinal evolution of parameters associated to morbidity and well-being, models for repeated measures will be performed using a random-effects model (linear or generalized linear) along with fixed effects for descriptive data (eg, gender, age, body mass index, type of contract [full-time, part-time], professional roles [unskilled, skilled, mid-level workers, and senior executives] and occupational sector [commercial activities and service, health and social services, manufacturing/blue collar industries, finance officers]) taking into account within and between participant variability and company variability. All effect sizes will be presented with 95% confidence intervals.

When appropriate, comparisons between subgroups described above will be performed. Typical statistical tests will be applied: chi-square or Fisher exact tests for comparisons between groups from categorical parameters and analysis of variance or Kruskal-Wallis test for quantitative variables. The Shapiro-Wilk test will be used to assess normality, and the Fisher-Snedecor test to assess homoscedasticity. For censored data, the time-to-event curves will be estimated with the use of the Kaplan-Meier method. Comparisons will be performed by log-rank test. Then, Cox proportional-hazards regression models will be considered to study the prognostic factors in a multivariate situation by backward and forward stepwise modeling on the factors considered significant in univariate analysis and in accordance with parameters of clinical relevance [83,84]. The proportional-hazard hypothesis will be verified using Schoenfeld’s test and plotting residuals. The interactions between possible predictive factors will also be tested. Results will be expressed as hazard ratios and 95% confidence intervals. Considering repeated correlated censored data, marginal models may be preferred.

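### The short-term aim is worded as a demonstration of improvement, but no outcome, time point or comparator among 11 subcategories is named to decide it

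*Protocol article*

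**What the plan says.** The Objectives section states: "The shorter term objectives will be to demonstrate that WittyFit improves parameters of well-being and morbidity based on three major health-related behavioral categories". The Abstract also speaks of demonstrating improvement, but labels this a feasibility objective. On design, the Abstract says: "This is an exploratory interventional cohort study in an ecological situation"; the Ethics section repeats that description.

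The Behavioral Outcomes section gives the content of the three categories:

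- "Physical well-being investigates nutrition, physical activity, sleep, and musculoskeletal function" (4 subcategories).
- "Mental well-being explores stress and mood" (2; addiction is to be added later and is not counted here).
- "Work-related health questions explore job strain, latitude/decision-making, work organization and tasks, social support, and recognition" (5).

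On timing, participants are prompted for a general "visual analog scale from the main categories and major subcategories every 15 days and the more detailed questionnaires every 6 months". Participation has no end date (Participants section).

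On the comparison, Analyses of Shorter Term Objectives says that "analyses will include comparisons with historical cohorts and literature and within the paired data from individual participants". It adds random-effects models for the repeated measures. The Sample Size Calculations section begins its figures with: "Considering an effect size of 0.33, a 2-tailed type I error fixed at a=0.001 to take into account multiple comparisons". It then gives one number for paired comparisons and another for intergroup comparisons. Overall Statistical Analyses makes every test two-sided and treats P<.05 as significant. The word *primary* is attached only to the long-term mortality objective.

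**The concern.** To demonstrate an improvement, a plan must say beforehand which result would count. This article gives a list of parameters and several comparators, and ranks none of them. If stress improves, sleep does not change and job strain worsens, the text does not say whether the short-term aim has been met.

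The sample size does not settle the matter. The effect size of 0.33 is introduced by reference to computer-based interventions on eating and nutrition, weight and fitness, mood, stress, and productivity. It is attached to no single WittyFit outcome.

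At stake is the meaning of a positive result. In an open-ended study with accumulating data, the outcome that carries the claim could be picked once the data are visible. The label exploratory would permit an open list of outcomes, but it does not fit an aim worded as a demonstration.

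**Working it through.** **1. The plan's own sample size.** Inputs from Sample Size Calculations: ES 0.33, two-sided alpha .001, correlation .5 for paired data, power above 95% (paired) and above 80% (intergroup). With correlation .5 the SD of the difference is √(2(1 − 0.5)) = 1 SD.

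- Paired: n = ((3.2905 + 1.6449)/0.33)² = 223.7, so 224; stated 225.
- Intergroup: n per group = 2 × ((3.2905 + 0.8416)/0.33)² = 313.6, so 314; stated 311.

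Both agree with the stated figures to within about 1%. The sizing is therefore sound for one generic contrast at .001. It does not identify which contrast that is.

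**2. Number of candidate outcomes.** 4 + 2 + 5 = 11 current subcategories.

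**3. Error rates at the stated analysis threshold.** Assume no true change, 11 tests at one time point and two-sided P<.05. Independent tests give:

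- at least one significant result: 1 − 0.95¹¹ = 43.1%;
- at least one significant improvement: 1 − 0.975¹¹ = 24.3%.

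The article gives no correlation between subcategories, so a range is assumed, using equicorrelated normal test statistics:

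| Assumed correlation | At least one P<.05, either direction | At least one apparent improvement |
|---|---|---|
| 0 | 43% | 24% |
| 0.3 | 37% | 19% |
| 0.5 | 30% | 15% |
| 0.8 | 18% | 9% |

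For one pre-named outcome the corresponding rates are 5% and 2.5%.

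**4. The same at .001.** Independent tests: 1 − 0.999¹¹ = 1.1%. At correlation 0.5 the rate is about 0.9%. At this level false positives are well controlled.

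**5. Three category scores, unadjusted, at .05.** Independent: 1 − 0.95³ = 14.3%; at correlation 0.5, about 13%. Reducing 11 subcategories to three scores helps, but does not remove the need for a rule.

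**6. What is left out.** No rate is given for testing several waves separately. The article models the repeated measurements jointly, so treating each wave as its own test would not represent its plan.

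**The case against.** **The full protocol may name a primary outcome.** The article points to an original protocol in Multimedia Appendix 1, which is not shown, and an analysis plan may exist. This stands as a limit: the point concerns what the article fixes. But the article has its own Outcomes, Objectives and Sample Size sections, and a protocol article normally states there what decides an objective.

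**The study is exploratory and the objective one of feasibility.** Both labels are in the text and carry weight. If they govern, an open list of outcomes is acceptable, and the wording of the aim has to change. They cannot stand beside an aim to demonstrate improvement without a statement of which applies.

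**The error rates depend on .05.** This is correct. The .001 in the sample size paragraph was chosen with multiplicity in mind and would hold 11 tests near 1%. But it appears only in that paragraph, while the analysis section sets P<.05 for all tests. Neither level says which result answers the objective.

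**A stronger reading to avoid.** A reader might infer that a gain in any one parameter at any wave would count as success, with error rates growing at every 6-month wave. The article states no such rule. Its objective speaks of parameters in the plural across three categories, which would equally fit a rule requiring all three to improve, and its random-effects models use the waves together. The fault is that the rule is undefined, not that a lax rule is written down.

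**Conclusion.** The concern holds in a limited form. The article sets out to demonstrate short-term improvement but designates no deciding outcome, time point or comparator among 11 current subcategories, and it leaves the effect size of 0.33 unattached to any one of them.

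The table's rates are what the stated P<.05 rule would allow if all 11 subcategories were tested at one time point and any of them could support the claim. They rest on no true change and on equal correlations assumed between 0 and 0.8. They are not a forecast of how the analysts will proceed. Adopting .001 would remove the numerical inflation but not the freedom to choose the deciding measure afterwards. The matter should be corrected; it does not invalidate the data collection or the sample size arithmetic.

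**What to change.** Before the outcome data are analysed, and with a statement of whether any have been examined since enrollment began in January 2016, do one of the following.

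- **(a) One deciding contrast.** Name a within-person change in one outcome already collected, at a fixed time such as 6 months, estimated from the planned random-effects model. Link the ES 0.33 calculation to it.
- **(b) One score per category.** Define one score for each of the three categories at that time. Test them by Holm or in a fixed order, state the family level, and reconcile it with the .001 used for the sample size.

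Under either option, report all other subcategories, waves and historical or literature comparisons as exploratory estimates with confidence intervals. If neither option is wanted, replace *demonstrate* with *explore* in the Abstract and Objectives.

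The cost is a few sentences and the disclosure about data already seen; no new participants or measurements are needed. The downside of (a) or (b) is that fewer outcomes can carry a confirmatory claim.

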### Confidentiality

All medical data (medical history, treatments, etc) will be only accessible from a carefully restricted WittyFit researcher access platform. All data are anonymous, and the name of the employee is never entered into the database. The database is implemented from a human resource–generated number, which is then automatically converted into another number in the WittyFit database. Data provided by employers (such as professional roles, occupational sector, type of contract, and absenteeism) are automatically associated with the human resource–generated number.

### Intervention

The WittyFit program offers tiered access to employee data for those with middle- and high-level management status.

#### Holistic Understanding of Workers

In contrast to other interventional software focusing on a specific aim (such as relaxation or identification of musculoskeletal disorders), WittyFit aims to promote health with a holistic understanding of workers (see Figure 1) based on continuous and updated scientific knowledge (evidence-based medicine). Feedback and counseling are provided on targets (relevant goals) screened from questionnaires (see Figure 2) using an e-learning platform or a “Did you know?” information approach based on personalized analyses of responses to questionnaires.

Each e-learning module (see Figure 3) is based on a 4-step approach used in pedagogy [68-70]: (1) answer a quiz (pretest), (2) understand the issue, (3) act on the issue, and (4) answer a quiz. The quiz is designed both for learning purposes and to evaluate workers [71]. The number of questions on the quiz is based on learning techniques [72]. The planned process involves the employees accessing their own personal data on a panel of indicators displaying their status, progress, and success. Employees may also contribute new ideas in the “digital idea box” and “likes” about ideas of others (see Figure 4). Employees may participate in company-specific surveys about healthful and feasible changes in the workplace. When some changes for employees are available to consider, a red dot will appear on the access button of the relevant topic.

**Figure 1 figure1:**
[figure not shown]
Screen capture of WittyFit: surveys foster a global understanding of workers.

**Figure 2 figure2:**
[figure not shown]
Screen capture of WittyFit: the homepage synthesizing the 3 major health-related categories in a personal dashboard with a menu structure on the left for access to visual analog scales, questionnaires, e-learning sessions, statistics, digital idea box, and polls.

**Figure 3 figure3:**
[figure not shown]
Screen capture of WittyFit: examples of e-learning sessions.

**Figure 4 figure4:**
[figure not shown]
Screen capture of WittyFit: the Digital Idea Box.

#### Manager Feedback

The second feature of WittyFit is that managers will receive anonymous feedback on the general state of health and problems encountered by their employees (see Figure 5) for whole or sectional divisions of the workplace if the sample size is sufficiently high (ratios of 1/10). Middle managers will be able to target specific actions such as promoting physical activity at work or workplace initiatives assisting employees to quit smoking. They will have access to the Best Practice database. Middle managers will also have access to the Forum Manager anonymous community to share their experience. They will have a Go/No Go functionality regarding the proposals in the digital idea box. If they are not in position to decide, the middle managers can propose an idea for the top management. Executive-level managers will have similar access as the middle managers, including indicators by division, location, department, age, seniority, gender, and occupational position. In addition, executive managers will have summaries of the turnover and absenteeism within the context of the visual analog scale data profiles. They can put in motion relevant ideas from the digital idea box and use the “What’s new?” editing tool to predict future changes to the work force in light of the nature of engagement of employees with the WittyFit software.

**Figure 5 figure5:**
[figure not shown]
Screen capture of WittyFit access for top management, including anonymous mean level of stress by location, department, age, gender, occupation, etc.

### Epidemiological Database

WittyFit has the capacity and innovation to strengthen evidence and build new knowledge on the relationships between lifestyle and health based on an increasing volume of epidemiological data.

### Connected Objects

Eventually, WittyFit will further evolve with the waves of connected objective measures of health and lifestyle, further increasing its data relevance, with the use of devices such as pedometers, heart rate monitors, accelerometers, and thermometers. Only volunteering workers will connect these objects to WittyFit. We will soon propose devices able to analyze these objective measures. For example, we have the expertise for objective measure of stress from heart rate variability or skin conductance [73-75].

### Multidisciplinary Project

WittyFit is building a spectrum of health-related data: work (shiftwork, sedentary workplace demands, specific and perhaps high-risk occupations), psychology and physiology, statistics modeling, public health, and medical health.

### Friendly Use

Ease of use of Wittyfit is our goal. When an action is needed, the user can follow a link from the homepage so there is no waste of time. Users can access previous answers but can only modify specific items. Questionnaires never exceed 12 to 14 questions. Users can stop answering questionnaire and resume later where they left off. At first log-in, completing all questionnaires takes approximately 30 minutes; to reduce the burden, we ask new users to complete all questionnaires over 2 to 3 weeks. Users can refer to an interactive guide that gives them advice on what’s next. WittyFit is available on any device connected to the Internet including computers, tablets, and smartphones; therefore, users can have access to WittyFit from where they want, including outside of their workplace. The gaming process is designed to increase the use of WittyFit by awarding points and badges for participation. The company is free to decide how to reward the best users with innovative strategies such as donations to nongovernmental organizations (see Figure 6).

